#### Secondary outcomes:

- (a) Index condition to multimorbidity cluster; and,
- (b) Multimorbidity cluster to death

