#### K. Definition of the Study population

Our study population comprises all acceptable patients permanently registered in any English General Practice that meet 'up to standard' CPRD GOLD data quality criteria between January 1, 2010 and December 31, 2020 and who ever had a recorded multimorbidity condition during this time frame. Patients are labelled as 'acceptable' if they meet acceptable data quality criteria for use in research.

With regards to the observational cohort design, our cohort will include all individuals aged 16 and over contributing data between January 1, 2010 and January 1, 2021. Each patient will have their Index Date, when the presence of multimorbidity will be defined. All included participants will be required to have 1 year of registration before the Index Date to maximise the record of prevalent cases across at least 12 months of registration. The patients will be followed from their Index Date until the earliest of dying, leaving the CPRD database, or the end of the follow-up period (1st Jan 2021).

We will use the CPRD Aurum as a validation data set, aiming to replicate our methods and validate our findings using the East London population, which comprises seven Clinical Commissioning Groups (Tower Hamlets, City and Hackney, Newham, Waltham Forest, Barking and Dagenham, Redbridge and Havering). The population specifications for Aurum will follow the same specifications as GOLD, i.e. in defining 'acceptable patients'. Considering that there is duplicate historical data for practices that have contributed data for both CPRD GOLD and Aurum, we expect CPRD to provide a bridging file to identify the overlapping practices and dates.

Our study population will be limited to those who are eligible for linkage.

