#### L. Selection of comparison group(s) or controls

In our observational cohort analysis, we will consider as case any patient who have multimorbidity (two or more long-term conditions listed in Appendix A). However, we will not have a comparison group since we aim to compare results across different levels of exposure rather than an unexposed versus exposed comparison.

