### Research Aims B and C)

Our research aims B and C will assess the trajectories of multimorbidity clusters of diseases and their relationship with prescribing. The main outcome of this analysis is the change of cluster the patients belong to over time. We will also consider mortality (date and cause of death) as a secondary outcome of the observational cohort. We will evaluate whether the progression of multimorbidity trajectories is predicted by known risk factors (e.g. high socioeconomic deprivation, smoking status, body mass index and clinical measures), and how it varies across different ethnic groups (White, Black African and Caribbean, and south Asian). Additionally, we have selected some indicators of health-seeking/risk behaviours, health care utilisation and life course variables. These variables are as follows:

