### Research Aims B)

To characterise the trajectory of multimorbidity clusters across the life course, we will identify clusters of multimorbidity and trace their evolution from single index conditions, and their trajectories across the lifecourse, including to death, over ten years. We anticipate focusing this analysis on up to 8 multimorbidity clusters, selected to ensure we generate new knowledge, e.g. clusters which include less-studied conditions such as cancer or HIV, as well as those where there is variation by ethnicity. We will follow the individuals within the selected clusters to identify the acquisition of new conditions and potentially changes in the cluster they belong to over time. Our analysis will consider how these trajectories to multimorbidity vary according to different 'index conditions', e.g. diabetes, HIV and cancer.

The assessment of the sequence of multimorbidity clusters an individual belongs to over the years will allow us to understand their disease trajectory over the period they were under observation and at different points in time. The multimorbidity cluster trajectories assessment will take into account the individuals' socioeconomic characteristics, potential risk factors and time dependent variables (e.g. clinical measurements, health seeking behaviours, health care utilisation, and life events).

[figure not shown]

We will identify individuals who share similar patterns of multimorbidity using clustering algorithms at different points in time. We aim to assess at least three points in time, with a ~five year interval between them (e.g. Jan 2011, Jan 2016 and Dec 2020). This time window will be subject to revision according to the available follow-up time in years of our study population. To evaluate the multimorbidity cluster trajectories, each individual will be assigned to the cluster with the highest membership degree in each point in time. We will be able to identify how the multimorbidity cluster changes in individuals from different age groups, sex and ethnicity.

We will estimate the association between the multimorbidity clusters and the risk to mortality in each follow-up period using Cox models adjusted by socioeconomic characteristics (age, sex, IMD) and risk factors (clinical measurements, health seeking/risk behaviours, health care utilisation, and life events) some of which are time dependent variables (e.g. BMI, blood pressure, lipids, HbA1c).

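### The single Index Date in section K does not give secondary outcome (a), index condition to multimorbidity cluster, a usable time origin, and sections H, K, L and N disagree on who is followed and from when

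*Protocol*

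**What the plan says.** Section K (Definition of the Study population) describes the observational cohort in its second paragraph: "our cohort will include all individuals aged 16 and over contributing data between January 1, 2010 and January 1, 2021". It then states "Each patient will have their Index Date, when the presence of multimorbidity will be defined". One year of registration is required before that date, "to maximise the record of prevalent cases across at least 12 months of registration". Follow-up runs only forward: "The patients will be followed from their Index Date until the earliest of dying", leaving the database, or the end of the study period.

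K's first paragraph defines the study population more narrowly. It limits it to people with a record, at some time in 2010 to 2020, of what it calls a *multimorbidity condition*.

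Three parts of the protocol depend on the path from one condition to several:
- Section C lists as secondary outcome (a) "Index condition to multimorbidity cluster". Secondary outcome (b) runs from cluster to death.
- Section M, Research Aims B and C: "We will evaluate whether the progression of multimorbidity trajectories is predicted by known risk factors".
- Section N, Research Aim B, undertakes to identify clusters and "trace their evolution from single index conditions", naming diabetes, HIV and cancer as examples.

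Three other places bear on who is followed. Section H includes everyone who meets the criteria, with or without multimorbidity, and says this is so that onset can be determined over time. Section L says "we will consider as case any patient who have multimorbidity" and that there will be no comparison group. Section N, Aim B, says that people already inside the selected clusters will be followed for new conditions and changes of cluster.

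**The concern.** A progression analysis needs an origin, the date a person becomes at risk, and a risk set that contains those who progress and those who do not. For outcome (a) the natural origin is the first listed condition, and the risk set is everyone with exactly one. For outcome (b) the origin is entry to a cluster. These are different dates in the same person, and the second comes after the event that outcome (a) is meant to study. Section K offers one date for both and describes it in terms of multimorbidity, not of the index condition.

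If follow-up in effect starts once multimorbidity is present, everyone followed has already had the outcome (a) event. The rate of progression from, say, HIV to a cluster then has no valid denominator, and factors that truly speed progression, such as deprivation or smoking, would look close to unrelated to it. A named secondary outcome and the determinants part of Aim B are at stake.

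**Working it through.** **1. The protocol's own calculation.** Section I gives n = Z²P(1−P)/d² = 1.96² × 0.272 × 0.728 / 0.002² = 190,174.6, which reproduces the stated 190,174. Multiplying by 1.10 gives the stated 209,191. This concerns the precision of a prevalence and has no bearing on outcome (a).

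**2. Two readings of the Index Date.**

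| | Onset of multimorbidity | Baseline date on which status is assessed |
|---|---|---|
| Support in the text | The date is tied to multimorbidity; N follows people within clusters | K's cohort is all individuals; the prior year is for finding prevalent cases; H includes everyone |
| People with one condition | Event already past in all who have an Index Date | At risk from the Index Date |
| Does time start at the index condition? | No, after it | No; prevalent single-condition people enter at differing, unstated durations |
| People with no condition at the Index Date | No Index Date unless they become multimorbid | No stated origin when the first condition appears |
| Can outcome (a) be estimated as written? | Sequences only, looking back | Movement is observable, but not timed from the index condition |

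Neither column gives outcome (a) the origin that its name implies.

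**3. Who is followed.**
- H: everyone eligible, with or without multimorbidity.
- K, first paragraph: people with a recorded *multimorbidity condition* during 2010 to 2020. If this means one listed condition, it drops the people with none whom H keeps, but it retains single-condition people. If it means multimorbidity, it conflicts with H and selects on the outcome. The period also extends past any individual Index Date, so eligibility can depend on later events.
- K, second paragraph: all individuals aged 16 and over.
- L: cases are multimorbid and there is no comparison group. Whether non-cases are followed is not said.
- N, Aim B: people within the selected clusters are followed.

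**4. Availability of the people needed.** Section I expects about 3 million acceptable GOLD patients. At the protocol's 27.2%, 3,000,000 × 0.272 = 816,000 would be multimorbid and 3,000,000 × 0.728 = 2,184,000 would not. The second group mixes people with one condition and with none. The 27.2% comes from a list of 36 conditions, so with 220 conditions the non-multimorbid share would be smaller. The population in H nevertheless contains non-progressors.

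**5. Illustration, onset reading only.** None of these hazards comes from the documents. Assume constant hazards of progression of h = 0.10 (exposed) and 0.05 (unexposed) per year, death or exit at 0.02 per year, and 10 years of observation. Let λ = h + 0.02.

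10-year risk = (h/λ)(1 − e^(−10λ)):
- exposed: (0.10/0.12)(1 − e^(−1.2)) = 0.582
- unexposed: (0.05/0.07)(1 − e^(−0.7)) = 0.360

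With the full risk set, the rate ratio is 0.10/0.05 = 2.0.

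Keep only those who progressed. The risk is then 100% in both groups, and mean time to progression = 1/λ − 10e^(−10λ)/(1 − e^(−10λ)):
- exposed: 8.333 − 4.310 = 4.023 years
- unexposed: 14.286 − 9.864 = 4.421 years

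Apparent rate ratio = 4.421/4.023 = 1.10. With hazards of 0.06 and 0.03 the mean times are 4.340 and 4.585 years, and the apparent ratio is 4.585/4.340 = 1.06 against a true 2.0. Simulation under the same assumptions gave 1.09 and 1.06, in line with these values apart from simulation error.

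**The case against.** A reader might infer that only multimorbid people are in the cohort, so that non-progressors are absent and outcome (a) cannot be estimated at all. The documents do not support that.
- H includes people without multimorbidity, expressly to determine onset.
- K's sentence on the Index Date directly follows one that admits all individuals aged 16 and over. A year's look-back for prevalent cases also fits a status assessment better than an onset date.
- Section M uses the same term, multimorbidity conditions, for the listed conditions for which code sets were built. K's restriction may therefore mean one listed condition.
- L defines a case, not cohort entry. Its remark on comparison groups disclaims an exposed-versus-unexposed contrast and does not remove anyone from a risk set.
- Aim B also assigns clusters at three or more calendar points, for example January 2011, January 2016 and December 2020. On the status reading, movement could be seen between them.
- Even on the onset reading, dated earlier records would allow sequences to be described.

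All of this stands. It removes the claim of certain selection on the outcome and confines the numerical illustration to one reading. It does not supply an origin for outcome (a): a calendar assessment point is not the date of the index condition either.

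It can also be said that the study is descriptive and hypothesis-generating, and that origins and risk sets are often left to an SAP, which is not shown here. But K does set cohort entry and the start of follow-up, in a form that does not fit one of the protocol's two secondary outcomes, and other sections point in different directions. That is a conflict in what is written, not detail held over. Calling the work hypothesis-generating does not help if real predictors would be pushed towards the null.

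**Conclusion.** The point holds in this form: section K's single Index Date does not serve secondary outcome (a) or the analysis of predictors of progression on either available reading, and H, K, L and N do not agree on who is followed and from when. On the onset reading, rates, risks and determinants of progression would be biased and only retrospective sequences would remain. On the status reading, the risk set exists but time is not measured from the index condition, and people who acquire their first condition later have no stated start.

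The size of any bias cannot be read from the documents. The fall from a rate ratio of 2.0 to about 1.1 rests on assumed constant hazards and on keeping progressors only, which the protocol does not clearly specify. Outcome (b) is affected only in that its start, cluster entry, should be stated separately. The sample size in section I is unaffected. The wording should be settled before the Aim B analysis begins.

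**What to change.** In section K:
- State what the Index Date is.
- State that *multimorbidity condition* means at least one listed condition, consistent with H.
- For outcome (a), start time at the first recorded index condition after at least 12 months' registration. Alternatively, admit prevalent single-condition patients by delayed entry, with time still counted from the condition. Keep everyone with exactly one listed condition at risk, including those who never progress, follow them to cluster entry, and treat death as a competing event.
- For outcome (b), start time at cluster entry.

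In section L, say that people with one condition who do not progress belong to the risk set for outcome (a). In section N, Aim B, say that following people within the selected clusters applies to cluster change and to outcome (b), and that outcome (a) follows single-condition people as H intends.

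The cost is protocol wording, carried into any SAP. No new data are needed, because the people are already in H's population. The price is that some prevalent cases are lost from outcome (a) under the 12-month rule, or that a delayed-entry analysis is needed to keep them.

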#### L. Selection of comparison group(s) or controls

In our observational cohort analysis, we will consider as case any patient who have multimorbidity (two or more long-term conditions listed in Appendix A). However, we will not have a comparison group since we aim to compare results across different levels of exposure rather than an unexposed versus exposed comparison.

#### M. Exposures, Outcomes and Covariates

##### Research Aim A)

This analysis does not have a specific exposure since it is a descriptive analysis of clusters of multimorbidity. Nevertheless, the clusters will be closely investigated according to covariables such as sex, age group, ethnicity (White, Black African and Caribbean, and south Asian) and socioeconomic deprivation levels (using the Index of Multiple Deprivation). The outcome of this analysis are the clusters of multimorbidity, defined using a list of 220 conditions (Appendix 1).

[figure not shown]

### Research Aims B and C)

Our research aims B and C will assess the trajectories of multimorbidity clusters of diseases and their relationship with prescribing. The main outcome of this analysis is the change of cluster the patients belong to over time. We will also consider mortality (date and cause of death) as a secondary outcome of the observational cohort. We will evaluate whether the progression of multimorbidity trajectories is predicted by known risk factors (e.g. high socioeconomic deprivation, smoking status, body mass index and clinical measures), and how it varies across different ethnic groups (White, Black African and Caribbean, and south Asian). Additionally, we have selected some indicators of health-seeking/risk behaviours, health care utilisation and life course variables. These variables are as follows:

#### 1. Primary exposures:

##### (a) Socioeconomic variables

- Index of Multiple Deprivation (individual and practice level)
- Ethnicity

##### (b) Health seeking/risk behaviours

- Smoking status
- Alcohol consumption
- Influenza vaccination

##### (c) Prescribing

- Continuous prescriptions: drugs within the same class prescribed 3 times or more per year: name, class and date of prescription.
- Polypharmacy: we will construct a derived variable, and expect to define this as the simultaneous use of five or more continuous prescriptions.

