### Research Aim C)

We will study prescribing and its relationship with multimorbidity clusters, and we anticipate focusing on the clusters under study in Research Aim B). We will investigate continuous prescriptions, defined as a prescription from within the same class repeated up to 3 times per year (allowing for drug switching between classes, and stockpiling between prescriptions). This will allow us to define polypharmacy, using the commonly used definition (the simultaneous, continuous prescription of 5 or more medications) but also to develop our own characterisation of the association between prescribing patterns and multimorbidity, e.g. the role of specific drugs. We will use several methodologies spanning machine learning and artificial intelligence which have not yet been used commonly in this field. The methods we expect to use overlap (in part) with our clustering approaches, and include: Association Rule Mining (ARM), or market-basket analysis; Latent Class Analysis (LCA), traditional iterative clustering methods (k-means, Hierarchical Cluster Analysis), as well as matrix factorisation methods. We will initially focus on ARM and factorisation methods, which are complementary and have proved successful in recent multimorbidity studies.

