of diagnosis code might as well include patients with morbidity, but missing diagnosis record. However, our study is limited by the quality of data recording.

- We are aware of the limitations of using primary care prescribing data in our analyses. In CPRD we will know when prescriptions are issued but not whether they are dispensed– this may make it difficult to explore questions around adherence (though we can assume to a certain extent that people who receive repeat prescriptions are taking their medications regularly). Additionally, we will not receive records of over-the-counter medication or in-hospital prescribing, however this is more typically short-term and therefore less likely to contribute polypharmacy.

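### A bare count of three issues a year makes repeated short courses 'continuous' and lets them count towards polypharmacy; the counting unit is unstated and sections M and N state opposite issue thresholds

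*Protocol*

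**What the plan says.** Section M, 1(c) Prescribing, sets the building block: "Continuous prescriptions: drugs within the same class prescribed 3 times or more per year", for which the drug's name, its class and the prescription date are kept. For polypharmacy it announces a derived variable that the team "expect to define this as the simultaneous use of five or more continuous prescriptions".

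Section N, Research Aim C, gives the definition again. A continuous prescription is there "defined as a prescription from within the same class repeated up to 3 times per year", with the qualifier "allowing for drug switching between classes, and stockpiling between prescriptions". Polypharmacy is "the simultaneous, continuous prescription of 5 or more medications".

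Section T accepts, to a certain extent, that "people who receive repeat prescriptions are taking their medications regularly". It also sets aside the lack of over-the-counter and in-hospital drug records, on the ground that such use tends to be short-term and so matters less for polypharmacy.

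Neither definition gives a minimum duration, a spacing or gap rule, a window for simultaneity, or a rule for two drugs of the same class.

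**The concern.** The section M rule tests only how often a class is issued. A class issued three times for three unrelated short episodes passes just as a class taken all year does. Section T shows that the plan does not regard short-term use as a main source of polypharmacy, yet the rule lets short-term primary care prescribing in.

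Polypharmacy is one of the outcomes named for Aims B and C in section G, is built from a primary exposure in section M, and is part of Aim C in section D. Repeated short courses plausibly occur more often in some disease clusters than in others, for example those with frequent infections or exacerbations. If so, the misclassification differs by cluster and could create or hide an association between cluster and polypharmacy. The protocol holds no data that show whether this happens.

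Two further gaps affect the same variable: the unstated counting unit for drugs that share a class, and the two opposite issue thresholds.

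**Working it through.** The protocol gives no figure for this variable, so there is none to reproduce. The check applies the two written definitions to invented prescribing patterns over one year.

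| Pattern (assumed) | Classes with ≥3 issues | Drugs belonging to those classes | Single drugs with ≥3 issues | Classes with 1 to 3 issues |
|---|---|---|---|---|
| A. Three short courses of one drug | 1 | 1 | 1 | 1 |
| B. Two long-term drugs in one class, 12 issues each | 1 | 2 | 2 | 0 |
| C. Five long-term drugs in four classes, 12 issues each | 4 | 5 | 5 | 0 |
| D. Four long-term classes, plus three short courses in a fifth | 5 | 5 | 5 | 1 |
| E. Three drugs of one class, issued once each | 1 | 3 | 0 | 1 |
| F. Five classes issued monthly | 5 | 5 | 5 | 0 |
| G. Five classes issued twice each | 0 | 0 | 0 | 5 |

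**Short courses.** Pattern A is one continuous prescription under section M. Exactly three issues also satisfies the literal section N wording, so settling the threshold does not remove this problem. Pattern D reaches five under section M if simultaneity means within the same year. With courses of 7 days (assumed), the fifth class covers 3 × 7 = 21 days, or 21/365 = 6% of the year. If simultaneity meant overlap on a given day, only those days could count.

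**Counting unit.** In pattern C the class count is 4, below the threshold, and the drug count is 5, at the threshold. Section M stores both name and class, so either count can be made from it. Counting every drug in a qualifying class brings sections M and N into line for pattern C, but it also turns pattern E, three drugs tried once each, into three.

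**Threshold direction.** Patterns F and G reverse. Monthly issue of five classes gives 5 under section M and 0 under the literal section N wording. Two issues of each of five classes gives 0 and 5.

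**Possible size of the short-course effect.** Assume that short courses of a class follow a Poisson distribution with rate λ per year. Then P(N ≥ 3) = 1 − e^(−λ)(1 + λ + λ²/2).
- λ = 1: 1 − 0.3679 × 2.5 = 0.080
- λ = 1.5: 1 − 0.2231 × 3.625 = 0.191
- λ = 2: 1 − 0.1353 × 5 = 0.323

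For a person on four long-term drugs who uses two such classes independently, the chance that at least one qualifies is 1 − (1 − p)²: 0.154, 0.346 and 0.542. These figures also assume the same-year reading.

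**Possible size of the unit effect.** If five drugs fall independently and equally over k classes, the chance that at least two share a class is 1 − ∏(k − i)/k for i = 0 to 4. This gives 0.419, 0.186 and 0.097 for k = 20, 50 and 100. These people would miss the threshold only if a class were counted once.

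**The case against.** A reader might infer that section M fixes the count at one per class, and so contradicts section N's count of medications. The documents do not support that. Section M keeps the drug name and never says that a class counts once. Section N also groups by class before it speaks of medications. The text can be read so that class decides whether the repeat test is met and named drugs are then counted. On that reading the sections agree at five in pattern C. What stands is that the unit is ambiguous, and that the ambiguity bites at the threshold.

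Both definitions also require simultaneity. A narrow window would remove most of the short-course effect, and a statistical analysis plan, not shown here, might set one. This limits the size of the effect. It does not answer the point that section M itself labels three short courses as continuous. Only the polypharmacy wording is provisional there; the rule for continuous prescriptions is not hedged.

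It is fair to add that the study is declared descriptive and hypothesis-generating, and that Aim C will first use association rule mining and factorisation methods, so polypharmacy is not its only measure. It remains a named outcome.

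A tempting remedy is to drop short-course classes such as anti-infectives. That would be harmful. HIV is a named focus for cluster selection (sections B, E and N), and section T lists chronic hepatitis among the included conditions. A blanket exclusion could remove long-term antiviral treatment from the count in the very clusters that the study targets.

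**Conclusion.** The concern holds in three parts. First, the section M rule admits repeated short courses as continuous, against the plain sense of the term and against section T. They can supply the fifth prescription towards polypharmacy if simultaneity is read as within a year. Second, the unit for drugs sharing a class is unstated. Third, the issue thresholds in sections M and N point in opposite directions and must be reconciled.

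The ranges of 15% to 54% (short courses) and 10% to 42% (shared classes) depend entirely on assumed rates, independence, an equal spread over classes and, respectively, the same-year and once-per-class readings. They should not be taken as the share of this cohort that would be misclassified. The first range concerns only people already on four long-term drugs who use two short-course classes. That the error differs by cluster is plausible but not shown. The definition should be corrected before polypharmacy is derived; the study design is not affected.

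**What to change.** Write one definition and use it word for word in section M, 1(c), and section N, Research Aim C.

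- Add to the issue count a condition that the issues be spread over the year, using the prescription dates already planned, or that they reach a minimum total of days supplied where that is available. The date condition is the weaker of the two, since short courses that happen to fall evenly across the year still pass. Exclude no whole drug class.
- State once whether two drugs of one class count as one or two, and report the other unit as a sensitivity analysis.
- Reconcile the two issue thresholds, and state the window for simultaneity.

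The cost is the rewording of two passages and some coding. The spacing condition needs no new variable. The days-supplied condition may need duration or quantity fields, since section M lists only name, class and date. Some intermittent long-term use will be missed; a sensitivity analysis with the bare count now in section M would show how much.

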## G. Study Design

**Research Aim A)** We will use a cross-sectional design. For this analysis, we will include data from all active 'acceptable patients' ( $\geq 16$  years of age) who were permanently registered to English General Practices between 1 January 2010 and 31st December 2020. The practices included will be those contributing with 'Up to standard' data during the study timeframe.

**Research Aims B and C)** We will use an observational cohort design. Considering that this is a hypothesis-generating study, our main aim is not to compare exposed and unexposed groups of patients, instead, we will evaluate the development of multimorbidity clusters to generate hypotheses on their trajectory and to help identify homogeneous groups of patients who may share similar prognosis and health care needs. We will assess these trajectories throughout the follow-up period and look at the potential factors that affect them, including where specific life course events occur, and in the context of specific prescribing patterns (particularly polypharmacy). The outcomes of this analysis will be the development of multimorbidity clusters of diseases through the years, polypharmacy and mortality. We will censor the patients who have transferred out of their practice during the follow-up period.

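### Polypharmacy is defined only as a yes/no at five drugs; the number of continuous prescriptions should be analysed with it

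*Protocol*

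**What the plan says.** Section G (Study Design, Research Aims B and C) states: "The outcomes of this analysis will be the development of multimorbidity clusters of diseases through the years, polypharmacy and mortality". Section M lists prescribing as item (c) under "1. Primary exposures". That item has two entries. The first is drug-level: "Continuous prescriptions: drugs within the same class prescribed 3 times or more per year: name, class and date of prescription". The second is the derived polypharmacy variable, which the team "expect to define this as the simultaneous use of five or more continuous prescriptions".

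Section N, Research Aim C, uses the same cut, "the simultaneous, continuous prescription of 5 or more medications", and describes it as the definition in common use. It then goes further: "but also to develop our own characterisation of the association between prescribing patterns and multimorbidity, e.g. the role of specific drugs". On methods it says: "We will initially focus on ARM and factorisation methods, which are complementary and have proved successful in recent multimorbidity studies". Latent class analysis, k-means and hierarchical clustering are also listed.

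No section makes the number of simultaneous continuous prescriptions an outcome or an exposure in its own right.

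**The concern.** Nobody can be classed as having five or more continuous prescriptions without counting them. The count therefore exists, at least as an intermediate step, before the cut is applied, and the cut then discards most of what it holds. People on 5 and on 15 drugs are recorded alike, as are people on none and on 4. Two clusters, or two ethnic groups within a cluster, could differ in drug burden and still show similar proportions with polypharmacy.

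The protocol's own reasoning points to the count. Section E motivates the prescribing work by earlier evidence relating multimorbidity to how many prescriptions people have, and asks for finer analysis of prescription data. Section M keeps the parallel burden measures, hospital admissions and primary care consultations, as yearly numbers. Drug burden is the one dichotomised.

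At stake are the resolution and precision of one derived variable, mainly in the smaller clusters and ethnic strata that Aims B and C intend to study.

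**Working it through.** **The plan's own figure.** The protocol gives no sample size or power for polypharmacy. Its one calculation, in section I, is for the prevalence of multimorbidity: 1.96² × 0.272 × 0.728 / 0.002² = 190,174.6, which reproduces the stated 190,174. It does not bear on this point.

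**Inputs.**
- From the protocol: the cut at five; an HIV prevalence of 0.09% and about 3 million acceptable GOLD patients (section I). These give 0.0009 × 3,000,000 = 2,700 people, used only as a plausible size for a small group.
- Assumed, because the protocol is silent: a negative binomial drug count X with mean m and dispersion k = 2 (variance m + m²/k); m from 3 to 10; a second group whose mean is 5% or 10% higher; two-sided 5% test.

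**Formulas**, with n per group and ratio of means r:
- Cut: p₁ = P(X ≥ 5) at mean m and p₂ at mean rm; z = (p₂ − p₁) / √{[p₁(1 − p₁) + p₂(1 − p₂)] / n}.
- Count: z = ln r / √{[1/m + 1/k + 1/(rm) + 1/k] / n}.
- Power ≈ Φ(z − 1.96).

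**One case in full** (m = 8, r = 1.05, n = 2,700):
- Cut: p₁ = 0.6554, p₂ = 0.6743, standard error 0.01285, z = 1.47, power 31%.
- Count: ln 1.05 = 0.04879, standard error √(1.24405 / 2,700) = 0.02147, z = 2.27, power 62%.

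**Power, cut versus count, k = 2:**

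| Mean | Share at 5 or more | 2,700 per group, 5% | 2,700 per group, 10% | 500 per group, 10% |
|---|---|---|---|---|
| 3 | 23% | 36% vs 51% | 88% vs 97% | 27% vs 38% |
| 6 | 53% | 36% vs 60% | 87% vs 99% | 27% vs 46% |
| 8 | 66% | 31% vs 62% | 81% vs 99% | 23% vs 48% |
| 10 | 74% | 27% vs 64% | 74% vs 99.5% | 20% vs 50% |

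The 500 is also an assumption, standing for an ethnic stratum of a small cluster. With 2,700 per group and a 20% difference, both analyses have about 100% power.

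**A second set of assumptions.** For a 10% higher mean, the share of the count's information that the cut keeps is:
- Poisson: 59% at mean 3, 61% at mean 5, 37% at mean 7, 16% at mean 9, 3% at mean 12.
- Negative binomial, dispersion 3: 65%, 58%, 46%, 35% and 23% at the same means.

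For 90% power at mean 9, the cut needs 1,533 people per group against 246 (Poisson), or 2,945 against 1,020 (negative binomial).

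**The common building block.** Count and indicator both depend on what makes a prescription continuous. Section M requires at least three issues of the same class per year. Section N, Aim C, describes the same class repeated at most three times per year. These are opposite bounds and overlap only at exactly three.

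**The case against.** The strongest reply is that the protocol does not rest its prescribing work on this indicator. Drug-level continuous prescriptions are a separate primary exposure, and Aim C starts with association rules and factorisation of drug patterns. A reader might infer that prescribing differences between clusters are lost; the documents do not support that. This part of the reply stands, and the loss is confined to the polypharmacy variable. It does not remove the point, because those methods describe which drugs occur together and none is stated to analyse the number per person.

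A reader might also see a conflict with section L, where "we aim to compare results across different levels of exposure rather than an unexposed versus exposed comparison". That sentence explains why there is no comparison group. It does not govern how polypharmacy is coded.

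Nor is residual confounding by drug burden a supported criticism. The only regression specified is the Cox model in section N, Aim B, and prescribing is not among its listed adjusters.

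Three further replies reduce the weight. The cut is provisional and conventional, in a study that calls itself descriptive and hypothesis-generating. Polypharmacy is not among the primary or secondary outcomes in section C and is called an outcome only in section G. The power figures rest on assumed distributions and group sizes: 2,700 is a number of people with HIV, not a cluster size, and the protocol plans no two-group comparison of that size. All three stand as limits on how much this matters. They do not make the binary as informative as the count.

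**Conclusion.** The point holds for the polypharmacy variable alone. The protocol fixes its form twice as a cut at five and nowhere analyses the count from which it is made.

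Under the assumptions shown, the count has more power throughout: 51–64% against 27–36% for a 5% difference with 2,700 per group, and 97–99.5% against 74–88% for a 10% difference. In very large clusters both are near 100%, and what remains is that the indicator cannot show any gradient above or below five. The direction does not require most patients to exceed the cut: at mean 3, only 23% do and the count still gains. A reader might assume that most multimorbid patients are above five, but the documents give no figure for that share, nor any mean or dispersion, so the actual size of the loss is unknown.

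This is a modest, nearly free improvement. It does not threaten the main outcomes. The conflict between sections M and N over what is continuous needs no assumption and must be settled before either form of the variable is defined.

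**What to change.** In section M, 1(c), and section N, Research Aim C:

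- State that the number of simultaneous continuous prescriptions will be analysed: with a count model (for example negative binomial) where it is an outcome, and as a continuous or spline term wherever it is used as an exposure.
- Report the five-or-more indicator with it, so that results remain comparable with published work.
- In the same edit, reconcile the two definitions of a continuous prescription, so that the count and the indicator rest on one rule.

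The cost is slightly more analysis and reporting. No new data are needed, because the count has to be computed before the cut can be applied.
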